#### 5.4 Evaluation criteria

Primary evaluation criterion: The clinical safety of Eurartesim® will be evaluated through the analysis of the adverse events captured by the health agent that will contact each patient at Day 5 ( $\pm 2$  days) after starting of Eurartesim® treatment. Any AE referred (frequency, intensity, action taken, outcome) will be recorded on the specific section of the patient chart as well as those identified in the referring hospitals or through adverse events spontaneously reported by the patient detected at the health facility within 28 days after the first medication intake. Special attention will be given to the serious adverse events (SAE) and/or adverse events (AE) classified as severe and/or adverse events of special interest (AESI) (see section 8.5).

- Main secondary evaluation criteria: The cardiac and biological safety of Eurartesim® will be intensively evaluated in the nested subset of **about 1,000** patients to evaluate the effect of the administration of Eurartesim® on blood biochemistry (BUN, Creat, ALT/AST, Bilirubin, electrolytes (K+ and Cl)), full blood count (Hb, RBC, WBC and differential count)) as well as ECG parameters. In case of clinically significant abnormalities, the examination will be repeated. The occurrence of adverse events will be recorded during these visits. Concentrations of PQ will be evaluated in a subgroup of about 200 patients at baseline (Day 1 before drug administration), Day 3 (before the last drug administration and 3-4 hours after the last drug administration), and Day 7. QTc interval and piperaquine concentration relationship will also be investigated.

#### Other secondary evaluation criteria

- The results of the thick blood smears systematically prepared at Day 1 in the subset of **about 1,000** patients will allow a retrospective categorization of patients in the two subsets of those confirmed to be infected with *Plasmodium falciparum* malaria and those infected with other *Plasmodia*. A comparison of the tolerability profiles between these sub-populations will be carried-out.

- The relationship between the occurrence of adverse events and the administration of concomitant medications will be also evaluated in the subset population of **about 1,000** patients.

## 6. STUDY POPULATION AND PATIENT SELECTION

### 6.1 Sample size

**About** ten thousand patients with suspected malaria diagnosed by WHO criteria and possibly by a RDT/microscopy will be enrolled and a subset of **about 1,000** patients with a microscopy diagnosis of *Plasmodia* (any species) will be studied more intensively

### 6.2 Selection criteria

#### 6.2.1 Inclusion criteria

- Uncomplicated malaria (*Plasmodia* of any species) diagnosed as per national policies and in line with WHO recommendations (a history of fever in the previous 24 h and/or the presence of anaemia, for which pallor of the palms appears to be the most reliable sign in young children). Confirmation of malaria by a parasitological diagnosis with RDT is encouraged but its absence does not prevent patients from being enrolled.
- Age  $\geq 6$  months and weight  $\geq 5$  kg.
- Capability of taking an oral medication.
- Ability and willingness to participate based on signed informed consent (a parent or a guardian has to sign for children below 18 years old), or on verbal consent given in front of a witness signing the informed consent, and access to health facility. The patient is to comply with all scheduled follow-up visits.

#### 6.2.2 Exclusion criteria

- Known allergy to artemisinin or to piperaquine.
- Known pregnancy.
- Lactating women should be excluded if other anti-malarial treatments are available
- Complicated malaria.
- Taking medicinal products that are known to prolong the QTc interval. These include (but are not limited to):
  - Antiarrhythmics (e.g. amiodarone, disopyramide, dofetilide, ibutilide, procainamide, quinidine, hydroquinidine, sotalol).
  - Neuroleptics (e.g. phenothiazines, sertindole, sultopride, chlorpromazine, haloperidol, mesoridazine, pimozide, or thioridazine), antidepressive agents.
  - Certain antimicrobial agents, including agents of the following classes:
    - macrolides (e.g. erythromycin, clarithromycin),
    - fluoroquinolones (e.g. moxifloxacin, sparfloxacin),
    - imidazole and triazole antifungal agents,

- and also pentamidine and saquinavir.
- Certain non-sedating antihistamines (e.g. terfenadine, astemizole, mizolastine).
- Cisapride, droperidol, domperidone, bepridil, diphemanil, probucol, levomethadyl, methadone, vinca alkaloids, arsenic trioxide.
- Have taken a DHA/PQP dose in the previous four weeks.
- Family history of sudden unexplained death, or personal or family history of predisposing cardiac conditions for arrhythmia/QT prolongation (including congenital long QT syndrome, arrhythmia, QTc interval greater than 450 milliseconds with either Bazett or Fridericia correction).

### 6.3 Enrolment procedure

#### 6.3.1 Investigational Sites

The Study will be conducted at selected health facilities in the following HDSS, Manhica, Rufiji, Dodowa, Kintampo, Navrongo, Nouna **and Nanoro**.

#### 6.3.2 Patient selection

At least 10,000 **treated** malaria cases will be enrolled. A subset of about 1,000 patients will be assessed more closely. Each patient will be included once.

A patient will be included in the study in case he/she meets the selection criteria of the protocol and agrees to participate. In particular, in order to enter the study, the patient should accept that one drop of blood is taken for the preparation of a thick blood smear, that the community health agent contact him/her at home, that the data collected during those visits are registered and analyzed and finally that, in case of an SAE and/or an AE classified as severe and/or an AESI (see section 8.5) should occur he/she has to contact immediately the community health agent or the HDSS, directly.

The subset of **about 1,000** patients will need to accept to be strictly monitored at the health facility or HDSS, where a capillary blood sample is taken in order to prepare a thick blood smear, a venous blood sample is collected for chemistry, full blood count and PQ concentration assessment (in all the 1000 patient subgroup), and a triplicate ECG recording is performed before the start of the treatment. Furthermore, he/she has to agree to be visited again on day 3 and day 7 after start of the treatment, to run all the evaluations foreseen by the study protocol.

#### 6.3.3 Patient numbering

Each patient will be identified at the study site by a 7 digits number, referred to as patient ID number. The first digit is the HDSS number, the following two digits are identifying the recruiting health facility and the last four digits will identify the patient enrolment number. Each number will be unique and, in case a patient discontinues the study before the end of the follow-up period, his/her number will not be assigned to another patient.

A second number (nested number) will be assigned to the patients of the nested subset of **about 1,000** patients. This number will be of 4 digits and a chronological recruitment order will be followed in each site.

## 7. STUDY PROCEDURE AND DATA COLLECTION

### 7.1 Visit planning

The inclusion in the study will be performed in the HDSS centre or in one of the associated health facilities, at Day 1 during the consultation.

The first follow-up contact with the patient **enrolled in the main group** will be performed at Day 5 ( $\pm 2$  days), always after administration of the last Eurartesim® dose, by the village community health agent.

In addition, the patients will be requested, in the event of any unusual significant symptom experienced during the 28 days following the treatment prescription, to visit their village community health agent (CHA) or contact directly the health agent who followed him/her during the study.

In case of occurrence of a SAE, an AE classified as severe or an AESI (see section 8.5) or if requiring medical care, the patient will be transferred to the study designated health facility by the village community health agent in order to receive care for his/her symptoms (this will be an unforeseen visit) and to provide more detailed information on the event.

In the subset of **about 1,000** patients that will be monitored more closely, they will go back home with a questionnaire in order to collect information about the food they eat from D1 to D3 and they will be asked to come to the health facility (HF) at D3 for directly observed treatment (DOT) administration of the 3rd dose.

In this subset, patients will have to come to the health facility site for a final visit at D7.

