#### 3.2 Eurartesim®

Eurartesim® is a fixed-dose combination product composed of dihydroartemisinin (DHA) and piperaquine phosphate (PQP) for the oral treatment of uncomplicated *Plasmodium falciparum* malaria. Eurartesim® contains DHA, to which all malaria strains are susceptible and to which drug resistance has not been reported. The long-term efficacy of Eurartesim® is secured by the presence of PQP. PQP is a second anti-malarial compound with a different mechanism of action and much longer half-life. Eurartesim® appears to offer significant benefits over existing licensed malaria treatments and is in line with current WHO treatment policy recommendations.

Two pivotal trials on the efficacy of Eurartesim® on treatment of uncomplicated *Plasmodium falciparum* malaria have been conducted in Africa and Asia, showing a high rate (>95 %) of treatment success. The Eurartesim® registration dossier has been submitted to EMA authorities and it got a centralized marketing authorization.

Evaluating possible drug-related side effects in patients with malaria and treated in the endemic countries can be difficult. There is considerable overlap between treatment-related symptoms and signs, and those of malaria (such as fever, anaemia) and concomitant illnesses (such as viral infections and parasitic infestations). Other reported AEs have been headache, vomiting, abdominal pain, asthenia, and cough.

The potential for Eurartesim® to prolong the QTc interval was investigated in parallel groups of healthy volunteers co-administered with high (~1,000 Kcal) or low (~400 Kcal) fat/calorie meals or in fasting conditions. Compared to placebo, the maximum mean increases in QTcF following Eurartesim® administration were 45.2, 35.5 and 21.0 msec, respectively, on day 3. Such QTcF prolongation observed under fasting conditions lasted between 4 and 11 hours after last dosing on day 3; afterwards, the mean QTcF prolongation compared to placebo decreased to 11.8 msec at 24 hours and to 7.5 msec at 48 hours. No healthy subject dosed in fasting conditions showed a QTcF greater than 480 msec, or an increase over baseline greater than 60 msec. The number of subjects overpassing these thresholds were 3 and 10 out of 64, respectively, for the low fat/calorie condition and 3 and 14 out of 40 for the high fat/calorie

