condition. No subject had a QTcF value greater than 500 msec in any of the dosing conditions.

More details about Eurartesim® can be found in the SmPC of the product.

DHA is very rapidly absorbed, the Tmax being about 1-2 hrs after single and multiple dosing. DHA bioavailability resulted higher in malaria patients than in healthy volunteers, possibly because malaria *per se* has an effect on DHA disposition, which may reflect malaria-associated impairment of hepatic function, causing an increase in DHA bioavailability (reduction of hepatic first pass effect) without affecting its apparent elimination half-life, which is absorption rate limited.

Piperaquine (PQ), a highly lipophilic compound, is slowly absorbed. In humans, it has a Tmax of about 4-5 hours after single and repeated dose. Due to its slow elimination, PQ accumulates in plasma with an accumulation factor of approximately 3 after the scheduled multiple dose treatment of three days. In healthy volunteers, PQ exposure is increased approximately 3-fold when administered with a high fat/high calorie meal. This effect is of clinical relevance because PQ is responsible for the effect of Eurartesim® on QT interval. Accordingly, Eurartesim® should be administered with water far away from meals.

DHA is principally converted to  $\alpha$ -DHA- $\beta$ -glucuronide ( $\alpha$ -DHA-G). Studies in human liver microsomes showed that DHA was metabolised by the UDP-glucuronosyltransferase (UGT1A9 and UGT2B7) to  $\alpha$ -DHA-G with no cytochrome P450-mediated metabolism. *In vitro* drug-drug interaction studies revealed that DHA is an inhibitor of CYP1A2, therefore there is the potential for DHA to increase plasma concentrations of CYP1A2 substrates.

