## 5.3 Drug prescription and dosing

The patients will be instructed to take Eurartesim® (DHA/PQP) with a dose regimen of one administration every 24 hours over a period of three days, i.e. at Day 1, then after 24 hours (Day 2) and after 48 hours (Day 3) from the first administration.

The dose will be based on body weight **as depicted in the table below**. Two strengths of Eurartesim® will be provided to facilitate the dosing in children and adults: 20/160mg and 40/320mg of DHA and PQP respectively.

| Body weight (kg) | Daily dose (mg)                                          | Number of tablets per dose |                  |
|------------------|----------------------------------------------------------|----------------------------|------------------|
|                  |                                                          | 20/160mg DHA/PQ            | 40/320mg DHA/PQ  |
| 5 to <7          | 10 mg DHA and 80 mg PQP                                  | ½ tablet            |                  |
| 7 to <13         | 20 mg DHA and 160 mg PQP                                 | 1 tablet            |                  |
| 13 to <24        | 40 mg DHA and 320 mg PQP                                 |                            | 1 tablet  |
| 24 to <36        | 80 mg DHA and 640 mg PQP                                 |                            | 2 tablets |
| 36 to <75        | 120 mg DHA and 960 mg PQP                                |                            | 3 tablets |
| 75 to <100       | 160 mg DHA and 1280 mg PQP                               |                            | 4 tablets |
| > 100            | There are no data on which to base a dose recommendation |                            |                  |

The patients will be instructed to take Eurartesim® with water, at least three hours before or three hours after food intake (i.e. three hours after the previous food intake with no food intake for the following three hours after Eurartesim® administration).

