### 7.2.3 Follow-up visits/contacts and clinical tolerability follow-up questionnaire

At Day 5 ( $\pm 2$  days) (after administration of the last Eurartesim® dose) following the inclusion date, the community health agent (CHA) will contact the patient at home. A further visit at the patient's home will be scheduled by the community health agent in all the cases in which the information collected during the telephone contact should be considered incomplete or unreliable ones.

He/she will then fill-in the second part of the chart (in triplicate) and report:

- His/her own 4 digit identification number (first two digits are the number of the health centre he/she is attached followed by a 2 digit number which will be assigned to him/her when the study starts).
- Date of the visit/contact.
- Clinical condition (recovered status or continuation of the illnesses).
- Compliance with the prescribed Eurartesim® treatment and in case, number of tablets of Eurartesim® not taken; an explanation of the reason why the treatment was not followed should be provided.
- Description of the symptoms experienced by the patient in case of a positive answer to the question: *“Have you noticed any unusual event/symptom since your last visit at the centre?”* Collect date of first manifestation of this/these event(s), symptom(s), intensity, treatment dis-/continuation, and evolution, in the specific section of the patient chart dedicated to the collection of Adverse Events.
- Current treatments, if taken.

In case, during his/her contact, the CHA assess that an occurred event is serious and/or severe, or detects an adverse event of special interest (see section 8.5), he/she should contact the HA and transfer the patient to the health facility in order to be examined. If necessary in the opinion of the HA, he/she should contact the investigators so that they can visit the patient and exactly define the status of the event and the causality. If the adverse event belongs to the cardiovascular category, an ECG will be performed. In addition, a thick blood smear will be prepared (for future analysis). In that event, a specific adverse event report form will be completed by the HA or the investigators.

The patient will receive first care treatment. In case any other treatment is prescribed by a HA staff or the study doctor, it will be reported on the patient chart.

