### **9.2 Analysis in the whole sample**

#### **Analysis in the whole sample and in the Subset population**

The statistical analysis will be mainly descriptive. The estimates of the incidence of adverse events will be based on crude rates. All estimates will be complemented with appropriate 95% confidence intervals.

The adverse events shall be regularly coded using MedDRA before database lock.

All SAEs and AESIs will be reviewed centrally by an independent safety monitoring panel.

Incidences will be computed on the following classes of AEs, overall and by SOC/PT:

- All AEs
- Serious AEs
- Serious AEs related to study treatment
- AEs of special interest (AESIs)
- AEs which caused early discontinuation of Eurartesim®
- AEs related to Eurartesim® treatment

Specific analyses will be carried-out on the AESIs. Correlation analyses will be carried-out in order to verify if their occurrence is more frequent with the previous/concomitant use of other drugs (specific classes to be determined in the statistical analysis plan), including antimalarials, in presence of co-morbidity (specific classes to be determined in the statistical analysis plan), or in presence of parasitaemia.

Compliance will be computed in the whole population and in the subset of **about 1,000** patients, calculating for each patient the ratio between the number of tablets taken and the number of tablets that the patient should have taken. Two groups of patients shall be described: compliant = 100% treatment compliance and non compliant = other cases. The safety profile of compliant vs non-compliant patients will be compared.

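### The main group's one described adverse-event contact may fall within hours of the third dose, so the solicited look-back is uneven and can end before peak exposure

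*Protocol*

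**What the plan says.** Treatment is given "at Day 1, then after 24 hours (Day 2) and after 48 hours (Day 3) from the first administration" (protocol, section 5.3). For the main group, section 7.1 schedules the follow-up contact at Day 5 ± 2 days, "always after administration of the last Eurartesim" dose; section 7.2.3 repeats this condition. Neither section states a minimum interval after the dose.

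Under section 5.4 the primary criterion rests on adverse events "captured by the health agent that will contact each patient at Day 5" ± 2 days, together with events found in referring hospitals and events reported by patients within 28 days of the first intake. At the contact the agent asks: "Have you noticed any unusual event/symptom since your last visit at the centre" (section 7.2.3).

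On exposure, section 3.2 gives a piperaquine Tmax "of about 4-5 hours after single and repeated dose", about threefold accumulation over the three-day course, and a fasting QTcF prolongation that "lasted between 4 and 11 hours after last dosing on day 3".

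On analysis, section 9.2 says: "The estimates of the incidence of adverse events will be based on crude rates".

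**The concern.** The clause on the last dose fixes the order of events but not the distance between them. Day 5 minus 2 is Day 3, the day of the third dose. A patient telephoned an hour after swallowing it has been followed up according to protocol, yet the question put to that patient only looks backwards. Symptoms that begin at or after the peak then depend on the patient coming forward or reaching a hospital.

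That is a weaker route for mild events. Section 7.1 asks patients to come forward for a symptom that is both unusual and significant, whereas the contact question asks about anything unusual. Mild dizziness or itching, both on the list of signs of special interest in section 8.5, could be elicited at a contact and never volunteered. In the main group only the first dose is supervised (section 5.3), so the text places no staff member with the patient after the third.

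What is at stake is the primary estimate. One crude incidence would combine patients who were asked almost nothing about the period after the last dose with patients asked about four days of it.

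**Working it through.** **1. The plan's own figure.** Section 9.3 states a 95% probability of identifying an event with incidence 1/3,000. With P = 1 − (1 − p)^n and p = 1/3,000:
- n = 10,000: P = 0.964
- n = 9,000 (the main group, section 7.3.1): P = 0.950

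The statement reproduces. The n needed for exactly 95% is ln(0.05)/ln(1 − 1/3,000) ≈ 8,986.

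**2. The window on a clock.** Take the first dose as hour 0.
- Third dose: 48 h.
- Piperaquine peak after it: 48 + 4 to 48 + 5 = 52-53 h.
- QTcF prolongation: 48 + 4 to 48 + 11 = 52-59 h.
- Earliest permitted contact: any time after 48 h on Day 3.

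A contact in the first 4-5 hours after the third dose precedes the peak. One in the first 11 hours comes before the reported QTcF period has ended.

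**3. Spread of the solicited look-back.** Contacts run from Day 3 to Day 7.
- From the first dose: 3 − 1 = 2 days to 7 − 1 = 6 days.
- From the last dose: 3 − 3 = 0 days to 7 − 3 = 4 days.

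**4. Day numbering.** Day 5 after starting could be read as five elapsed days, which gives Day 4 to Day 8, and the bracket in section 7.2.3 could be read as counting from the last dose. But section 6.3.2 has nested patients "visited again on day 3 and day 7 after start of the treatment", and that day 3 is the day of the third dose. The requirement that the contact follow the last dose would also be unnecessary if the window never reached Day 3.

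**5. Possible size (assumptions, not in the documents).** Let f be the share of the 9,000 contacted on Day 3, and m the share of those patients' events that start after the contact and are never captured. Assume the underlying event rate does not depend on contact day. The main-group incidence is multiplied by 1 − f·m. The effective n for detection is 9,000(1 − f·m) + 1,000.

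| f (patients) | m | Incidence multiplier | P(detect 1/3,000) |
|---|---|---|---|
| 0.05 (450) | 0.25 | 0.988 | 0.963 |
| 0.05 (450) | 0.5 | 0.975 | 0.962 |
| 0.20 (1,800) | 0.25 | 0.95 | 0.959 |
| 0.20 (1,800) | 0.5 | 0.90 | 0.952 |
| 0.20 (1,800) | 1 | 0.80 | 0.935 |
| 0.40 (3,600) | 0.5 | 0.80 | 0.935 |
| 0.40 (3,600) | 1 | 0.60 | 0.882 |

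f = 0.20 corresponds to contacts spread evenly over the five days. m = 1 is a bound rather than a scenario, because events after the first two doses would still be elicited on Day 3. Detection falls below 0.95 only if f·m exceeds (10,000 − 8,986)/9,000 = 0.113.

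**The case against.** The case for leaving the rule alone has several parts.

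- **Capture does not stop at the contact.** A reader might infer that events after an early contact are lost. The documents do not support that. All patients are asked to report for 28 days, regional hospital data are collected regularly (section 7.2.3), and patients agree to make contact at once for serious or severe events and events of special interest (section 6.3.2). This stands, and it confines the exposure mainly to non-serious events.
- **There may be a later enquiry.** Section 7.1 calls this the first contact, and the whole-sample flow chart marks adverse-event recording at the end of the 28-day follow-up. No text describes a scheduled contact at that time, so the mark cannot be counted as one. It is a discrepancy to reconcile.
- **QT effects are studied elsewhere.** The nested subset has ECGs before and 3-4 hours after the third dose and again on Day 7, with adverse events solicited at both visits. Section 8.5 notes that QTc prolongation usually gives no symptoms, and the 4-11 hour figure comes from fasting healthy volunteers. So the QTcF timing does not show that cardiac findings will be missed. It shows only that an early contact precedes a period of high exposure.
- **The gain from a later contact is partial.** Events that start after any contact depend on unsolicited capture. A minimum interval recovers only those that start between the early contact and the later one and would otherwise go unreported.
- **Early contacts may be few.** The target is Day 5, and charts reach the agents at least twice a week (section 10.1). Contacts need not spread evenly, and nothing in the documents shows that the mix will differ between sites.

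None of this supplies a reason for allowing a contact within hours of the last dose.

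**Conclusion.** The point holds as a weakness in a stated rule, correctable at little cost. The window permits a Day 3 contact before the peak that the protocol itself reports, and the solicited look-back after the last dose varies from about 0 to 4 days within one crude incidence. The expected consequence is some under-capture of non-serious events in main-group patients contacted early. The nested subset is not affected, since it is seen on both Day 3 and Day 7.

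The size cannot be established from the documents; the figures in the table rest entirely on the assumed f and m. The tempting stronger conclusion, that the primary safety objective or the 95% detection claim fails, is not supported. Detection stays at 0.952 with 20% of contacts on Day 3 and half of those patients' events uncaptured. It drops below 0.95 only when the product of the two shares passes about 11%. The duty to report serious and special-interest events at once makes that less likely for the events that matter most.

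The conclusion assumes that Day 1 is the day of the first dose. If Day 4 to Day 8 was meant, the concern about the peak falls away, but the text still needs a clarifying sentence.

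**What to change.** In sections 7.1 and 7.2.3, and wherever the window is repeated, require the main-group contact at least 24 hours after the last dose, which is Day 4 to Day 7 on the present schedule. The solicited period after the last dose then runs from about 1 to 4 days. State the day-numbering convention in the same sentence.

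Tabulate adverse-event incidence by contact day as a sensitivity check on the crude rate. Section 7.2.3 already records the contact date, so no new data are needed, and the table would also show how many contacts fell early.

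Reconcile the flow chart's adverse-event mark at the end of the 28-day follow-up with the text: either describe the contact or explain that it means unsolicited reports only.

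The cost is one protocol sentence and a contact window of four days instead of five. Because section 7.3.3 counts a patient not reached within the window as lost to follow-up, slightly more patients may be lost. The change concerns data collection only and leaves treatment as it is.
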